## Abstract

**Introduction:**

Higher education, particularly university, is a challenge for many students that can lead to their mental health being seriously affected. The stress to which they are subject throughout their time at university can lead to anxiety and depression. “Third wave” psychotherapies, including compassion-based therapy, have been used to improve psychological outcomes, such as stress, anxiety, emotional distress and well-being. There are some signs that third wave psychotherapies reduce psychological distress in university students, but more and higher-quality studies are needed. In this randomised controlled trial (RCT), we hypothesise that the provision of attachment-based compassion therapy (ABCT) will be more effective than an active control group based on relaxation therapy for improving psychological distress in university students.

**Methods and analysis:**

A two-arm RCT will be conducted involving 140 university undergraduate and postgraduate students from the University of Zaragoza and the National University of Distance Education (UNED) who reside in the autonomous community of Aragon, Spain. Interventions with either ABCT or relaxation therapy will be implemented, with an allocation ratio of 1:1 between groups. Both interventions will last six weeks and consist of six weekly group sessions lasting 1.5 h each. Data will be collected before and after the intervention, and there will be a follow-up at six months. The primary outcome will be psychological distress at post-intervention. Secondary outcomes will be depression, anxiety, stress and burnout symptoms, affectivity and emotional regulation. Attachment style, experiential avoidance, compassion (for others/oneself) and mindfulness skills will be measured as potential mechanistic variables. Intention-to-treat analysis will be performed using linear mixed regression models. The clinical significance of improvements will be calculated. Potential side effects will be monitored by an independent clinical psychologist.

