### Sample size

The sample size estimation was calculated based on the assumption that the ABCT group would be able to obtain intermediate effects when compared to the active control condition based on relaxation therapy. In order to determine this, we considered a standardised difference between trial arms on the main outcome (psychological distress, measured by the Depression, Anxiety and Stress Scale (DASS-21) total scale) of 0.5, which is the more conservative estimation observed in a previous similar study that included university students and delivered a third wave psychological intervention based on six meditation sessions (Modrego-Alarcon et al., 2021), and is usually considered a common rule of thumb of clinically significant change (Norman et al., 2003). Considering a power (1-β) of 0.80 for a two-tailed contrast and an α of 0.05 with a group allocation ratio of 1:1, we obtained a group size of approximately 64 subjects. Therefore, the total size of the required sample will be 128 voluntary participants from the university student population. Assuming a loss rate of around 30%, based on a previous similar study (Modrego-Alarcon et al., 2021), we have inflated the numbers so that the total sample size needed will be approximately 190 subjects, 95 in each group.

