### Recruitment

Recruitment of potential participants will begin as follows: (1) informative posters providing a brief explanation of the study will be displayed around the main campus of the University of Zaragoza at tutoring whose services are used by students of distance courses (for UNED students) and other places of interest for university students to encourage interested students to make contact via e-mail; (2) contact will be made with different student organisations to send informative e-mails to students. Each organization will send the message using e-mail lists, without providing the research group with any personal information; and (3) contact with local government agencies and media (e.g., newspapers) to disseminate information about the research study and provide a contact e-mail for any interested students.

Those students who make e-mail contact will be provided with more detailed information by means of a phone call or virtual meeting. A research assistant will explain the study and verify that the student meets the inclusion criteria. This contact will also specify the route by which the study information document is to be received, and a link will be provided to the baseline evaluation. All assessments which will be made online, both at baseline and in the subsequent follow-up measurements at the end of the intervention (post-treatment), and at six months, and the surveys will be completed online using SurveyMonkey^®^. Before beginning the baseline survey, the participants will be able to read the information sheet, accept the privacy terms and conditions of the website, and sign the informed consent form. The recruitment and baseline assessment process will continue until the required sample size is obtained.

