### Level of significance

An alpha level of 0.05 will be established using a two-tailed test.

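### The abstract gives a total of 140 participants, but the sample-size section needs about 190; with 140 randomised and the plan's own 30% loss, power would be about 69%

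*Protocol article*

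**What the plan says.** Three places in the protocol article bear on the number of participants.

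- Abstract, Methods and analysis: "A two-arm RCT will be conducted involving 140 university undergraduate and postgraduate students". No power or loss rate is given there.
- Methods, Sample size: the assumed standardised difference on the DASS-21 total score is "of 0.5, which is the more conservative estimation observed in a previous similar study". The error rates are set by "Considering a power (1-β) of 0.80 for a two-tailed contrast and an α of 0.05 with a group allocation ratio of 1:1". The result is about 64 per group, 128 in total. After an allowance for loss of around 30%, the section ends: "we have inflated the numbers so that the total sample size needed will be approximately 190 subjects, 95 in each group".
- Methods, Recruitment: "The recruitment and baseline assessment process will continue until the required sample size is obtained". No number is attached.

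The Level of significance section repeats the two-sided 5% level, so the sizing inputs agree with one another. The only conflict is over the total.

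**The concern.** The two totals differ by 50 participants, which is 50/190 = 26% of the larger one. Wording such as *approximately* cannot cover a gap of that size, and no step in the sizing leads to 140. It is not the requirement before loss, not that requirement inflated for 30% loss, and not the total that the section states.

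The recruitment target is one of the figures a reader, an ethics committee or a trial team takes from a protocol, and many take it from the abstract. A team that stopped at 140 could point to the published abstract in support. With loss as the plan expects, the chance of missing an effect of the assumed size would rise from the planned 20% to about 31%, and a non-significant primary result would be harder to interpret.

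**Working it through.** **Inputs, all from the Sample size section unless noted.** Standardised difference d = 0.5 (SD taken as 1); two-sided α = 0.05; power 0.80; allocation 1:1; loss around 30%; inflated total about 190. The total of 140 is from the abstract.

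**Step 1. Reproduce the plan's figure.** With the normal approximation, n per arm = 2(1.96 + 0.8416)² / 0.5² = 62.8, so 63. The two-sample t-test (noncentral t) gives 63.77, so 64 per arm and 128 in total. The plan's figure reproduces.

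**Step 2. Inflate for loss.** 128 / (1 − 0.30) = 182.9, so 183, or 184 for equal arms. The stated 190 is somewhat higher and would absorb a loss of 1 − 128/190 = 32.6%. That fits a rate described as around 30%, and the rounding is on the safe side.

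**Step 3. Look for a source of 140.** The requirement before loss is 128. Correct inflation gives 183 to 184. The common mistake of multiplying by 1.3 gives 128 × 1.3 = 166.4, so 167. None of these is 140.

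**Step 4. Loss that 140 can absorb.** 1 − 128/140 = 8.6%, less than a third of the assumed rate.

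**Step 5. Power under the plan's own loss.**

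| Randomised | Remaining at 30% loss | Per arm | Power at d = 0.5, t-test | Power, normal approximation |
|---|---|---|---|---|
| 140 | 98 | 49 | 68.8% | 69.7% |
| 190 | 133 | 66.5 | 81.6% | 82.2% |

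The normal-approximation entry for 140 is Φ(0.5 × √(49/2) − 1.96) = Φ(2.475 − 1.96) = Φ(0.515) = 0.697. With 49 per arm the t-test has 80% power only for d of about 0.57.

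**Step 6. Sensitivity of the 140 figure to loss (t-test, d = 0.5).**

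| Loss | Per arm | Power |
|---|---|---|
| 0% | 70 | 83.6% |
| 10% | 63 | 79.5% |
| 20% | 56 | 74.6% |
| 25% | 52.5 | 71.8% |
| 30% | 49 | 68.8% |

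**The case against.** The strongest reply is that the Methods are sound and the abstract contains one stray number. The sizing reproduces, 190 with 30% loss gives about 82% power, and the Recruitment section comes directly after the section that ends at about 190. This largely stands. Read in sequence, the Methods point to about 190, so it would be too strong to say that the recruitment end point is undefined. What remains is that the abstract contradicts this target and the Recruitment section gives no figure to settle it.

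A second reply is that 69% is conditional. It takes 140 as the number randomised, applies the whole 30% loss by the post-treatment assessment (the Sample size section does not say to which time point the rate refers), and uses a simple two-sample comparison. This also stands. If 140 were the number analysed, power would be about 84%, although 140 would still match neither 128 nor 190. The Main analysis section plans a repeated-measures mixed model, whose precision depends on a baseline-to-post correlation that the article does not give. As an illustration, with 49 per arm a change-score contrast has power of 61%, 69% and 78% at assumed correlations of 0.4, 0.5 and 0.6. The sizing used no such correlation, so the two-sample figure is the one comparable with the plan's 80%.

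Three stronger readings are tempting, and the document does not support them.

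- A reader might infer that the plan claims 80% power for 140. It does not. The 80% belongs to the 128 participants before the loss allowance, and the abstract states no power.
- A reader might call 190 an arithmetic error because 128/0.70 is 183. Both the loss rate and the total are given as approximate, and rounding up only adds power.
- A reader might infer that two totals invite a test at 140 and another at 190, with an inflated type I error. No interim test is planned, no staggered outcome data are described, the statistical expert is to be blinded, and the monitoring committee's oversight of survey results concerns participants' health.

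**Conclusion.** The point holds as an internal contradiction on the total sample size. The abstract's 140 and the Sample size section's total of about 190 are both current text and cannot both be the recruitment target. The derivation supports about 190. It does not support 140 at the assumed loss.

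The size of the problem, if 140 were followed, is a fall in power from about 82% to about 69% at d = 0.5, or a detectable difference of about 0.57 instead of 0.5. This rests on 140 being the number randomised, on 30% being lost before the primary endpoint, and on the plan's two-sample sizing method. The contradiction itself, and the 8.6% limit on loss, rest on none of these beyond 140 being the number enrolled and 128 the number needed.

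**What to change.** State one recruitment target, as a number randomised, in the abstract, the Sample size section and the Recruitment section, so that the required sample size in the Recruitment section refers to an explicit figure.

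- If the target is about 190, replace 140 in the abstract. The sizing text can stay as it is.
- If the target is 140, change the Sample size section to match, and state that under 30% loss the power is about 69% at d = 0.5, or that the difference detectable with 80% power is about 0.57.

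The cost is one corrected figure in the first case and a less favourable power statement in the second. Neither changes the design, the outcomes or the analysis.

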**Ethics and dissemination:**

This study was approved by the Clinical Research Ethics Committee of Aragón. Participant data will remain anonymous, and results will be submitted to peer-reviewed open-access journals and disseminated via conferences.

**Clinical Trial Registration:**

ClinicalTrials.gov, identifier NCT05197595.

## Introduction

### Background and rationale

Recent studies show that university students commonly suffer from mental health problems (Auerbach et al., 2018; Karyotaki et al., 2020). It has been found that more than half of university students might suffer from depression, panic and/or generalised anxiety (Keyes et al., 2012). Anxiety levels increase during university years (Bewick et al., 2010), and the prevalence rates of psychological distress and mental health problems are significantly higher than those of the general population (Stallman, 2010; Jackman et al., 2022). There are numerous areas that can pose a challenge and increase stress for university students, such as financial status, health, love life, family and work/school relationships, and problems experienced by loved ones (Karyotaki et al., 2020). The main mental health pathologies found are depression and anxiety (Regehr et al., 2013), although some university students also report feelings of loneliness, difficulties with family and intimate relationships, and other interpersonal concerns (Conley et al., 2015). All these mental health problems may have psychological and social impacts, and they can also determine students’ ability to function in academic terms, leading to an increase in dropout rates (Dyrbye et al., 2010; Sharp and Theiler, 2018; Marôco et al., 2020), which presents a problem for themselves and for the institutions involved (Conley et al., 2015). Nevertheless, providing psychological tools is believed to be a promising way to enhance students’ resilience and minimise risks of mental health problems (Sharp and Theiler, 2018; Sheldon et al., 2021).

In recent years, there has been an increasing number of studies regarding so-called “third wave” cognitive-behavioural psychological techniques. Through the promotion of acceptance, mindfulness, cognitive defusion and compassion, these therapies seek to change the function of experience for the individual in order to enhance well-being (Hayes et al., 2006). Third wave therapies have demonstrated promising results in different areas related to people’s health and psychological well-being (Grossman et al., 2004; Khoury et al., 2015; Spijkerman et al., 2016; Kirby et al., 2017). A number of studies show that these techniques can reduce anxiety, stress and burnout, and increase psychological well-being in the university population (Regehr et al., 2013; de Vibe et al., 2018; Patel et al., 2018; Dawson et al., 2020). Nonetheless, although their results are promising, some of the studies have also been found to have low methodological quality and considerable heterogeneity of effects (Dawson et al., 2020).

Among third wave psychological techniques, mindfulness-based programmes (MBPs) have predominantly been studied for the prevention and treatment of depressive or anxiety symptoms, and they have also been used in clinical practice for the longest time (Parsons et al., 2017; Cladder-Micus et al., 2018; Goldberg et al., 2018). As examples of how this has materialised, we can see that the National Institute of Health and Care Excellence (NICE) UK guideline recommends an MBP for the prevention of relapses in depression (Kendrick and Pilling, 2012), and that some MBP adaptations for university students have been piloted with positive results (Medlicott et al., 2021). One of the implicit components of MBPs is compassion. However, the effectiveness of compassion-based programmes (CBPs), which use specific practices to develop compassion, is yet to be proven in non-clinical populations (Brito-Pons et al., 2018). A number of pilot studies that include explicit compassion practices and programmes based on compassion therapy have shown encouraging results; however, they were conducted using small samples and therefore require further replications (Arimitsu, 2016; Ko et al., 2018; Collado-Navarro et al., 2021; Martínez-Rubio et al., 2021). In the university population specifically, the efficacy of self-compassion is inconclusive as there is not a great deal of evidence (Dawson et al., 2020) that is consistent with the state of the art in the general population, meaning that further research is required (Kirby et al., 2017; Shonin et al., 2017).

CBPs propose meditative techniques and practices to develop (a) compassion for others, which arises from witnessing the suffering of others and having the desire to alleviate it (Goetz et al., 2010); and (b) self-compassion, which is this same desire but towards oneself (Neff, 2003). The attachment-based compassion therapy (ABCT) programme (García-Campayo et al., 2016; García-Campayo, 2020) seeks to promote compassion for others and self-compassion in individuals through the development of a secure attachment style. Although work on the attachment style has already formed part of some of the compassion programmes on which ABCT is based (Neff, 2003; Gilbert, 2009), ABCT makes the change towards a healthy attachment style the core of the therapeutic process. This programme has obtained satisfactory results by increasing self-compassion in healthy adults (Navarro-Gil et al., 2020) and reducing affective distress in patients with anxiety, depressive and adjustment disorders (Collado-Navarro et al., 2021), and its clinical usefulness with fibromyalgia patients has also been demonstrated (Montero-Marin et al., 2019; Santos et al., 2022), with results maintained in the medium term.

This present study will continue this line of research by assessing the effectiveness of an adapted six-week ABCT programme in the treatment of psychological distress in university students, compared with relaxation therapy. It will also evaluate the potential mediating role of attachment style, experiential avoidance [i.e., the unwillingness to experience painful thoughts and emotions (Berta-Otero et al., 2022)], compassion (for others/oneself) and mindfulness skills (i.e., an awareness of the present moment that is characterised by a non-judgmental attitude) in the intervention group, compared to the active control group based on relaxation therapy. There is some preliminary evidence to show that experiential avoidance, self-compassion and mindfulness skills having a potential mediating role in ABCT (Montero-Marin et al., 2019; Collado-Navarro et al., 2021; Lopez-del-Hoyo et al., 2022). However, there are no previous studies evaluating attachment style and compassion for others as putative mechanisms of ABCT, even though they are core constructs of the programme.

### Objectives and hypotheses

The main aim of this study will be to assess the effectiveness of a six-week ABCT programme, compared with an active control group based on relaxation therapy (including progressive muscular relaxation and guided imagery), for the reduction of psychological distress symptoms in university students. Secondary objectives are (a) to examine the effects of ABCT on anxiety, depression, stress and burnout symptoms, as well as positive and negative affect, and emotional regulation and (b) to analyse the possible mediating role of attachment style, experiential avoidance, compassion (for others/oneself) and mindfulness skills on improvements in the ABCT group, compared to the control group based on relaxation therapy.

The main hypothesis is that ABCT will be more effective than relaxation therapy to reduce psychological distress in university students at post-treatment. Secondary hypotheses are the following: (a) ABCT will be more effective than relaxation therapy for the improvement of anxiety, depression, stress and burnout symptoms, as well as positive and negative affect, and emotional regulation at post-treatment; (b) improvements in psychological distress, anxiety, depression, stress, burnout, positive and negative affect, and emotional regulation will be maintained at six-month follow-up; and (c) attachment style, experiential avoidance, compassion (for others/oneself) and mindfulness skills will have a mediating role on the improvements obtained in the ABCT group vs. the control group based on relaxation therapy.

### Trial design

This study will be a randomised controlled trial (RCT) comprising two parallel arms, with pre-treatment, post-treatment and six-month follow-up measurements, and a 1:1 allocation ratio between groups. University students in Zaragoza, Spain, will be randomly assigned to two different conditions: ABCT (intervention group) and relaxation therapy (active control).

## Methods

This protocol was designed in accordance with the Standard Protocol Items: Recommendations for Interventional Trials (SPIRIT) statement (Moher and Chan, 2014). The trial registration can be found at ClinicalTrials.gov NCT05197595 (January 19, 2022).

### Setting and study sample

We will recruit students from the University of Zaragoza and the National Distance Education University (UNED), both in Spain, who meet the following inclusion/exclusion criteria. Inclusion criteria: (a) over 17 years of age; (b) studying for an undergraduate or postgraduate (master’s or PhD) degree; (c) proficient in spoken and written Spanish; and (d) provide signed informed consent. Exclusion criteria: (a) over 30 years of age; (b) diagnosed with a disease that affects the Central Nervous System or a serious mental illness; and (c) consumption of recreational drugs or on medication that could affect the nervous system. Concomitant care will be permitted during the trial if treatment has been initiated previously and consists of a maintenance dose (no increments or psychological interventions will be allowed).

### Sample size

The sample size estimation was calculated based on the assumption that the ABCT group would be able to obtain intermediate effects when compared to the active control condition based on relaxation therapy. In order to determine this, we considered a standardised difference between trial arms on the main outcome (psychological distress, measured by the Depression, Anxiety and Stress Scale (DASS-21) total scale) of 0.5, which is the more conservative estimation observed in a previous similar study that included university students and delivered a third wave psychological intervention based on six meditation sessions (Modrego-Alarcon et al., 2021), and is usually considered a common rule of thumb of clinically significant change (Norman et al., 2003). Considering a power (1-β) of 0.80 for a two-tailed contrast and an α of 0.05 with a group allocation ratio of 1:1, we obtained a group size of approximately 64 subjects. Therefore, the total size of the required sample will be 128 voluntary participants from the university student population. Assuming a loss rate of around 30%, based on a previous similar study (Modrego-Alarcon et al., 2021), we have inflated the numbers so that the total sample size needed will be approximately 190 subjects, 95 in each group.

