### Interventions

Both groups will receive interventions with a duration of six weeks. Each session will be 90 min long and will be held in face-to-face groups. Before beginning the programme, participants will be given a paper copy of the information sheet and the informed consent form, and they will be able to raise any doubts they might have regarding the study.

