#### Attachment-based compassion therapy

The ABCT programme that will be used is a short adaptation of the University of Zaragoza compassion training programme (García-Campayo et al., 2016). Table 1 shows how the sessions are structured in terms of theory as well as formal and informal practices. Tasks to consist of practical exercises using audio recordings will be set for completion between sessions. The ABCT programme will be conducted by a clinical psychologist with experience in ABCT and third generation therapies.

**Table 1 tab1:** Adaptation of the ABCT programme (6 weeks).

Session 1	Preparing for compassion: kind attention.	Theory: the functioning of our brain, the reality of suffering: primary and secondary suffering, what is and what is not compassion. Formal practices: compassionate breathing and compassionate body scan, compassionate coping with difficulties. Informal practices: 3-Minute compassion practice, self-compassion journal, savour and thank you
Session 2	Discovering our compassionate world	Theory: compassion and mindfulness, self-esteem and compassion, fear of compassion. Formal practices: connect with affection, develop a situation or a safe place, compassionate gesture and phrases. Informal practices: the object that unites us to the world, compassion practice diary, what are we good at?
Session 3	Developing our compassionate world	Theory: mechanisms of action of compassion, efficacy of compassion, self-criticism. Formal practices: identify and develop the secure attachment figure, replace the critical voice with the compassionate voice. Informal practices: write a letter to the attachment figure.
Session 4	Understanding our relationship with compassion	Theory: attachment models, importance of these models in daily life. Formal practices: becoming aware of our attachment model, receiving affection from friends, indifferent and enemies. Informal practices: Letter to parents
Session 5	Working on ourselves	Theory: importance of affection towards oneself and towards others Formal practices: giving affection to friends and indifferent, giving affection to ourselves, reconciliation with our parents. Informal practices: three positive and three negative aspects of our parents, the largest sample of affection (in general and from our parents)

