#### Relaxation therapy

The progressive muscle relaxation programme proposed by Bernstein and Borkovec (1973) will be used. To match this programme to the ABCT programme, it will be adapted to six sessions, each lasting 90 min, with the addition of guided imagery. As in the previous case, tasks to consist of practical exercises using audio recordings will be also set for completion between sessions. The contents and structure of the sessions are described in Table 2. The relaxation program will be facilitated by a clinical psychologist with experience in relaxation techniques.

**Table 2 tab2:** Relaxation programme (6 weeks).

Session 1	Presentation of the group and the goals of relaxation Basic principles of progressive muscle relaxation Brief explanation of the initial procedure with 16 muscle groups Progressive muscle relaxation practice with 16 muscle groups Imagination training Identification of the sensations and difficulties of relaxation
Session 2	Share homework related experiences and doubts Theory of visualisation techniques Practice of progressive muscle relaxation with 16 muscle groups Visualisation Practice: The Orange Identification of sensations and difficulties of relaxation
Session 3	Share homework related experiences and doubts Brief explanation of the procedure with 7 muscle groups Practice of progressive muscle relaxation with 7 muscle groups Visualisation Practice: The Beach Identification of sensations and difficulties of relaxation
Session 4	Share homework related experiences and doubts Practice of progressive muscle relaxation with 7 muscle groups Visualisation practice: the landscape Identification of sensations and difficulties of relaxation
Session 5	Share homework related experiences and doubts Brief explanation of the procedure with 4 muscle groups Practice of progressive muscle relaxation with 4 muscle groups Visualisation practices: the globe and white light Identification of sensations and difficulties of relaxation
Session 6	Share homework related experiences and doubts Brief explanation of relaxation by evocation, relaxation by evocation + counting and relaxation by counting Relaxation by evocation + counting Relaxation by counting Mental relaxation and visualisation practice: the perfect day Identification of sensations and difficulties of relaxation

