### Main analysis

The effectiveness of the ABCT group vs. the control group based on relaxation therapy will be evaluated at post-treatment on the main DASS-21 total score, considered as a continuous variable. Multilevel mixed effects linear regressions will be carried out by means of a repeated measures design on an intention-to-treat (ITT) basis, using the restricted maximum likelihood (REML) method. Non-standardised slopes and 95% confidence intervals (95% CIs) for the “group × time” interaction will be provided, together with raw means (SDs) by group. Cohen’s *d* effect size (ES) will be calculated using the combined SD at baseline (Morris, 2008). ESs are considered small when *d* ≤ 0.2; medium when *d* = 0.5; and large when *d* ≥ 0.8 (Cohen, 1988).

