With regard to the strengths of this study, although compassion-based approaches show promise for treating the mental health of university students, this study will be one of the first RCTs to evaluate the efficacy of CBPs on university students’ mental health, and the first to verify the specific potential benefits of ABCT for this population. In addition, the study will make use of a randomised controlled design with a relatively large sample of university students and a medium-term (6 months) follow-up, as recommended by previous research on this population (Dawson et al., 2020). This will allow changes to be observed in the medium term and mediation analyses to be carried out. It is also important to point out that an active control group will be used, as recommended in research using contemplative programmes (Ma and Teasdale, 2004), since it allows possible changes in the variables to be attributed to the intervention and not to other factors, such as the attention shown by the instructor or the relationship with the group.

As limitations, we need to recognise that the use of self-report measures can be biased due to social desirability. Another possible barrier is the fact that these programmes require consistent home-based practice between sessions (Grossman et al., 2004). This can lead to the distraction of part of the sample due to fatigue or lack of commitment to the programme.

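### The 64 per arm behind the stated 80% power assumes independent participants, although both programmes are delivered in groups; therapy group should be a named level of the model

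*Protocol article*

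**What the plan says.** **Delivery.** Participants are randomised individually once baseline data are in (Randomisation, allocation, and blinding). The Interventions section then says, for both arms: "Each session will be 90 min long and will be held in face-to-face groups". The programmes run for six weeks.

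**Sample size.** The effect is a standardised difference, "measured by the Depression, Anxiety and Stress Scale (DASS-21) total scale) of 0.5". The remaining inputs are 80% power, a two-sided 5% level and equal allocation. The result is reported as follows: "we obtained a group size of approximately 64 subjects". This gives 128 in total, raised to about 190 (95 per arm) for a loss of around 30%. No therapy-group size, ICC or design effect appears.

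**Primary model.** The Main analysis section states: "Multilevel mixed effects linear regressions will be carried out by means of a repeated measures design on an intention-to-treat (ITT) basis". Estimation is by REML and the effect of interest is the group-by-time interaction. The random effects are not listed.

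**Facilitators.** For the compassion arm: "The ABCT programme will be conducted by a clinical psychologist with experience in ABCT and third generation therapies". For the control arm: "The relaxation program will be facilitated by a clinical psychologist with experience in relaxation techniques".

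**The concern.** Participants who meet in the same group for six weeks share a facilitator, a group climate and each other's company. Their outcomes can therefore be more alike than those of participants in different groups, even though randomisation was by individual. The Discussion accepts that such influences can move outcomes, since it names instructor attention and the relationship with the group as things the active control is meant to balance.

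Two things are at stake. The first is the planning figure: with any positive within-group correlation, 64 per arm carries less information than 64 independent people, and power at d = 0.5 is below what the calculation implies. The second is the primary inference: if the fitted model knows only about occasions within persons, its standard error for the arm comparison leaves out the between-group variance.

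**Working it through.** **Inputs from the protocol article (Sample size):** d = 0.5 (SD = 1), two-sided alpha 0.05, power 0.80, 1:1 allocation, 64 per arm, about 30% loss, 190 recruited.

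**Assumed, because the article gives neither:** planned groups of 12, so m = 12 × 0.70 = 8.4 completers per group; ICC from 0.01 to 0.10.

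**Step 1: reproduce the stated figure.** The two-sample t-test for d = 0.5 needs 63.77 per arm, rounded up to 64, and power at 64 is 0.801. The stated number is reproduced with a design effect of exactly 1.

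**Step 2: slack from rounding up recruitment.** 190 × 0.70 = 133, or 66.5 per arm, with power 0.816 if participants are independent. 66.5/64 = 1.04, so the slack absorbs a design effect of about 1.04.

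**Step 3: allow for clustering.** Design effect DE = 1 + (m − 1) × ICC = 1 + 7.4 × ICC. The standard error of the standardised difference is √(2 × DE/n), and power comes from the noncentral t with 2n − 2 df. If the group level is left out, the standard error is too small by a factor √DE and the actual type I error is about 2[1 − Φ(1.96/√DE)].

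| ICC | DE | Power, 64 per arm | Power, 66.5 per arm | Type I error if group level omitted |
|---|---|---|---|---|
| 0 | 1.00 | 0.80 | 0.82 | 5.0% |
| 0.01 | 1.07 | 0.77 | 0.79 | 5.9% |
| 0.02 | 1.15 | 0.75 | 0.76 | 6.7% |
| 0.05 | 1.37 | 0.67 | 0.69 | 9.4% |
| 0.10 | 1.74 | 0.57 | 0.58 | 13.7% |

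Put as a detectable difference, the 0.5 becomes about 0.5 × √DE: 0.52, 0.54, 0.59 and 0.66 at the four positive ICCs.

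**Step 4: sensitivity to group size.** At ICC 0.05 and 64 per arm, using the effective sample size n/DE, power is 0.67, 0.64 and 0.57 for m = 8, 10 and 15.

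**Step 5: few groups.** With m = 8.4 there are 64/8.4 = 7.6 groups per arm, hence about 2 × 7.6 − 2 = 13 df for the arm comparison. At ICC 0.05, power then falls from 0.67 to 0.61.

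**Step 6: baseline correlation.** None of the power figures above uses the baseline measurement. For a change contrast the variance is multiplied by 2(1 − r), where r is the assumed correlation between baseline and post-treatment. At r = 0.5 the factor is 1 and nothing changes; below that, power is lost. At r = 0.6 the factor is 0.8, and with 66.5 per arm power is roughly 0.85 at ICC 0.02 and 0.78 at ICC 0.05 (0.73 at ICC 0.05 with cluster df).

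**The case against.** **The model may already include therapy group.** A reader might infer from the repeated-measures wording that the model treats participants as independent and that its standard errors are too small. The article does not establish this. It calls the model multilevel, lists no random effects and excludes none, and the random-effects structure is commonly settled in an analysis plan, which is not shown. This objection stands, so the type I error figures are conditional. It does not reach the sample size, which is derived in full and reproduces only under independence.

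**The power loss rests on assumed inputs.** True: neither the ICC nor the group size is in the article. At ICC 0.01 with 66.5 per arm the shortfall is about one point, and a baseline correlation above 0.5 would recover some power. The article claims no such credit, however, and an efficient baseline adjustment would not correct type I error if the group level were missing.

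**Facilitator and arm.** A reader might also infer that each arm has its own single psychologist, so that facilitator is confounded with arm. The two descriptions make that plausible but do not settle it. The Randomisation section speaks of facilitators in the plural, and the Data collection and monitoring section of one psychologist in charge of the groups; number and overlap are left open.

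**The Discussion.** Nor does the Discussion claim to exclude differences in therapist skill. It says changes can be "attributed to the intervention and not to other factors, such as the attention shown by the instructor or the relationship with the group". That concerns non-specific attention and group contact, which an active group control does balance in kind.

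**Conclusion.** The sample-size part holds without condition: 64 per arm is an independent-participants figure for a trial delivered in groups, so the stated 80% contains no allowance for therapy-group clustering. The size of the loss depends on inputs the article does not give. With about 8.4 completers per group, power at 64 per arm is about 0.77 to 0.57 over ICC 0.01 to 0.10, and 0.79 to 0.58 with the 66.5 per arm that 190 recruits would leave. The small number of groups would lower these further, and baseline correlation could move them either way. The shortfall is minor near ICC 0.01 with small groups and material from about ICC 0.02 upward.

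The inference part is conditional. If no therapy-group level is fitted and the ICC is positive, the primary confidence interval will be too narrow and type I error will be about 6%, 7%, 9% and 14% at the four ICCs. Confounding of facilitator with arm is a possibility to be clarified, not a demonstrated flaw.

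**What to change.** 1. Record a therapy-group identifier for every participant, and name therapy group as a random effect in the primary and secondary models, with Kenward-Roger or Satterthwaite degrees of freedom (REML is already planned). Baseline is measured before allocation and the estimand is the group-by-time interaction, so the term should act on the post-baseline occasions. A random intercept shared by all occasions would largely cancel from that contrast.
2. Keep the planned N, state the expected group size, and restate power or the detectable d over ICC 0.01 to 0.10. If credit is taken for baseline correlation, state the assumed value.
3. State how many psychologists lead each arm and whether any lead both. If each arm is led by a single, different psychologist, add as a limitation that programme and psychologist effects cannot be separated; no model term can do so in that case.

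The cost is one recorded variable, one model term, somewhat wider intervals and a less favourable stated power. If a therapy-group level is already intended, item 1 costs one clause. The identifier has to be captured while the groups are running, so this should be settled early.
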